**F. Assessment of newborn**

1. Was there any need for Resuscitation of the newborn?

1=Yes

2=No?

2. If YES, what method was used for resuscitation?

1. Hanged the legs up,
2. Sprinkled cold water,
3. Mouth-to-mouth resuscitation
4. Slap the baby
5. Oxygen
6. Nothing

3. How was the weight of the newborn assessed?

1. Using a weighing scale
2. Estimation by looking at the size
3. Not done

4.1. If baby was premature how was assessment of prematurity done? (*If the response is NO then skip to section* ***G)***

1. Size of the baby
2. Told by health practitioner
3. Weight of the baby
4. Gestation age of the pregnancy
5. Anthropometric measurements

4.2. If Anthropometric measurements which one?

1. Feet
2. Arm
3. Head
4. thigh

5. Was there any special care given to this premature newborn baby?

1=YES

2=NO

6. If YES, can tick more than one option.

1. Extra warmth
2. Extra feeds
3. Frequent feeds
4. Less frequent bathing
5. No bathing at all
6. Keeping the baby indoor only
7. Specific traditional performances

**G. Care-seeking practices**

1. Did you make any postnatal visits to the health facility

1=Yes

2=No

1. How many postnatal visits so far have you made: 1,2,3,4
2. How early was the first visit
3. Within the first 24 hours after delivery
4. After 24 hours but before 72 hours
5. After 72 hours but before one week
6. After one week
7. After one month

**H. Care seeking**

Newborn immunisation

1. Is the newborn already immunised for

1. Polio zero 1=Yes 2=No
2. BCG 1=Yes 2=No
3. Polio 1 1=Yes 2=No
4. DPT HEB+Hib (pentavalent) 1=Yes 2=No

2.Did this newborn fall ill in the last three months? 1=Yes 2=No)

(*if NO conclude the interview*)

3. If yes how did you detect the illness? *(Circle all that apply)*

1. Failure to feed
2. Excessive crying
3. Less activity
4. Warm to touch

4.What immediate actions did you take? *(Circle all that apply)*

1. Attention to VHT
2. To Health centre
3. Seek medication at home
4. Traditional healers
5. Went to private clinic
6. Did nothing

5.How soon after the onset of illness did you seek for care?

1. Within one hour
2. Within six hours
3. Within 24 hours
4. After 24 hours
5. What in your view was the cause of illness?
6. Evil spirit
7. Some evil neighbours or relatives
8. Bad air
9. The infected umbilical stump
10. Acquired from place of delivery
11. Acquired from mother
12. No idea

Thank you for your time

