# Operational definition of terms

*Primary healthcare facility* The first contact point for formal healthcare - In this case the first contact for which pregnant women access antenatal care i.e. health centres II, III, IV and ANC services at hospitals

*Prenatal service* -as prescribed by the WHO history taking, physical examinations, laboratory investigation, prescriptions, administration of folic acid and Ferrous tablet, assessment for referral, dialogue and discussions about pregnancy, dangers in pregnancy, hygiene, immunisations and birth preparedness

*Technical maternal and newborn services*-more clinical services for example history taking, physical examination like palpation, drawing of blood samples, estimating pelvic adequacy and assessing for referral

*Less technical maternal and newborn services*-services of a promotional nature health education, counselling, birth preparation which entails dialogue and discussions with the pregnant women and their attendants/caregivers

*Individual ANC educational interventions*- information given to a pregnant woman attending ANC based on the unique problems or demands or needs that she presents with during the current pregnancy as opposed to uniform information provided to all prenatal women

*Consistent ANC visits*-timely and completed four ANC visits

*Health worker with a promotional profile* a health worker with a formal employment in the district health system, whose primary training is health prevention and health promotion, does not routinely take part in clinical services like physical examinations, prescriptions of medicines or surgery – in this case we refer to the Health Assistant (HA)

*Homecare practices*-care provided to prenatal women and newborn babies at home based on knowledge and perception of the care givers (elements of care considered in this study are: nutritional care for pregnant women, care for the cord, warmth for newborn babies, and initiation of breastfeeding and neonatal immunisation status)

*Elderly caregivers*-these are usually women in the households, about 50 years or older. They provide neonatal care and advice to family members within the household sometimes extending to the immediate neighbours. As opposed to TBAs, they are not transactional. They provide expert opinion and demonstrate actual care to postnatal women within the household or immediate neighbourhood

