### 4.3.6 Sampling procedure

For the quantitative survey, clusters will be stratified at the parish level; a list of all parishes will be obtained from the planning unit of the districts and 21 of them will be selected by a simple random technique using computer generated random numbers. At the parish level all lactating women with babies up to four months will be enumerated and a list generated. From this list a random sample proportionate to the total number will be identified and included in to the study. A written consent will be obtained from each participating lactating woman. Structured interview questionnaire (*see annex 6 for details*) will be administered by trained research assistants to all lactating women who provide consent to participate in the study.

This study will be conducted in Masindi and Kiryandongo districts in western Uganda. The questionnaire guide will be pre-tested twice to ensure suitability.

In the qualitative study, six elderly caregivers and six traditional birth attendants will be identified with the help of Local council I chairpersons or their representative from any of the 21 parishes sampled. Thirty lactating mothers stratified by age groups (adolescents 10-20 years and adults above 20 years) will be selected for In-Depth Interviews. All these will be individual interviews with open-ended questions. Written informed consent will be obtained from participants and the interview administered on acceptance (*see annex 7 for details of question guide)*. While we plan to interview a total of six elderly care givers and six TBAs the absolute number will be determined when we arrive at saturation point-when no more new practices and explanations are volunteered in subsequent interviews.

For the quantitative survey, lactating mothers having babies up to sixty days old (about two months) will be eligible for the study (see annex 5 for sampling procedure). The unit of analysis will be individual lactating mothers.

The number of lactating mothers to be interviewed per cluster will be allocated proportionate to the number of eligible lactating mothers available in the selected parishes.

Eligible lactating mothers will be identified by the use of village-bicycle scouts assisted by the local council I chairpersons (LC I) who will enumerate all eligible lactating mothers and generate a list; from this list a proportionate number from each of the parishes will be sampled using a simple random selection technique.

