## 4.3.8 Data collection and analysis plan

For both qualitative and quantitative data collection techniques research assistants familiar with the local dialect (Runyoro, Luo and Kiswahili) and possessing at least a degree in social sciences or public health having experience in social research will be recruited and trained for three days on the use of available tools and techniques. Pre-testing will be done twice to ensure suitability of the tools. Qualitative data from the Key Informant Interviews with elderly caregivers, TBAs and lactating women will be audio taped, transcribed verbatim and translated in to English, themes regarding prenatal and newborn homecare practices will be identified and described. A detailed description of the different care practices will be explored from elderly care givers and TBAs; these practices will be elaborated and broadly categorised according to prenatal, intra- and post-natal periods. The computer software program NVivo will be used. We will use content analysis to analyse data from TBAs and elderly caregivers and lactating mothers. Analysis will focus on making a detailed description of maternal and newborn care practices and the rationale for these care practices in the homes. For the In-Depth Interviews manual analysis of experiences of the different age groups adolescents (young adolescent ages 10-13 years; middle age 14-16 years and older adolescents ages 17-20) and older women over 20 years will be considered.

In the quantitative data with lactating mothers research assistants will be recruited and trained on the use of data collection tools; questionnaires will be pre-tested twice to ensue suitability of data collection tool; double data entry will be done in *epidata version 3.02*, cleaned and exported to *stata version 10.0* for analysis. Results will be presented in terms of descriptive statistics in proportions and rates. In a second level using bivariate data analysis, we will test for association between socio-demographic characteristics and the different maternal and newborn care practices using odds ratios and confidence intervals to test for levels of significance.

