## Annex 5 Sampling procedure for sub study two

Districts Masindi & Kiryandongo

Parishes (**21**)

**3** Villages per Parish

Lactating women with babies up to two months or sixty days at the time of the study **(823)**; regardless of parity and where delivery took place for semi-structured interview

Purposively identify **6** TBAs from any of the parishes and **6** elderly home caregiver from any of the parishes selected for KII interview;

Identify **30** lactating mothers from each of the following age groups: 10-13 years; 14-16 yrs; 17-19 yrs and 20 years and above for In-Depth Interviews

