**A: Socio-demographic characteristics**

1. Code number..........................................................................................
2. Name of household Head........................................................................
3. Age of Respondent in completed years (lactating woman)....................
4. Parity of respondent 1, 2, 3, 4, 5, over 5
5. Highest education level attained:
6. Non
7. Primary;
8. Secondary;
9. High school;
10. Tertiary;
11. Marital status:
12. Married
13. Single
14. Separated
15. Divorced
16. Widowed
17. What do you do for a living:
18. Nothing
19. Housewife
20. Farming/gardening
21. Selling in the market/petty trade
22. Business woman
23. Salaried
24. Did you attend any ANC during the last pregnancy:
25. Yes, 2. No
26. Number of ANC visits made with the last pregnancy:
27. 0,
28. 1,
29. 2,
30. 3,
31. 4
32. More than 4
33. Where did this last delivery take place:

**1)** Home;

**2)** Health facility;

**3)** On the way to health Facility

1. How old is the baby now? Age in completed weeks
2. 0-1 week **2)** 2-4 weeks **3)** 5-8 weeks **4)** 9-13 weeks
3. Number of living children: 1, 2, 3, 4, 5, 6, more than 6
4. Number of deceased children: 0,1, 2, 3, 4, 5, 6, more than 6

(*if deceased babies is* ***0*** *then skip to section* ***B***)

1. At what ages did the deceased children die?

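### Sub-study two records immunisation only as status at interview, without dates, in babies of unequal age, so the reported proportion depends on the age mix and the direction of its error against uptake by day 28 is unknown

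*Protocol*

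**What the plan says.** The protocol's operational definitions list the elements of homecare considered in the study, ending with "and initiation of breastfeeding and neonatal immunisation status". Section 4.4.6 treats the neonatal period as the four weeks after the pregnancy ends.

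In sub-study two the item is in Annex 6, section H: "Is the newborn already immunised for" Polio 0, BCG, Polio 1 and the pentavalent vaccine, each yes or no. No date of vaccination is requested. Section G asks for a count of postnatal visits ("How many postnatal visits so far have you made") and then when the first visit took place, in bands.

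The age of the babies is stated in two ways. Section 4.3.6 says that "lactating mothers having babies up to sixty days old (about two months) will be eligible for the study", and Annex 5 agrees: "Lactating women with babies up to two months or sixty days at the time of the study". Section 4.3.6 also says: "At the parish level all lactating women with babies up to four months will be enumerated and a list generated". Annex 6, section A, asks "How old is the baby now? Age in completed weeks", with bands of 0-1, 2-4, 5-8 and 9-13 weeks.

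For the analysis, section 4.3.8 states: "Results will be presented in terms of descriptive statistics in proportions and rates". It then plans bivariate odds ratios of care practices against socio-demographic characteristics. It states no minimum age, age-specific denominator or adjustment for the baby's age.

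**The concern.** A baby of three days who is not yet vaccinated and a baby of two months who was never vaccinated both give the answer no. The first may still be vaccinated within the neonatal period; the second can no longer be. A baby vaccinated on day 40 answers yes, although the dose came after the neonatal period. A single proportion over all ages adds these together, so it describes neither uptake by day 28 nor eventual uptake. It would change with the age mix of the sample even if practice did not.

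The same applies to the odds ratios: a characteristic that happened to be linked to the baby's age at interview would appear linked to immunisation. Sub-study two is meant to inform the educational messages of the trial, so a misleading level could misdirect emphasis. Dates that were not collected cannot be supplied by any later analysis plan.

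**Working it through.** **The plan's own figure.** Section 4.3.5 gives Z = 1.96, P = 0.42, Q = 0.58, design effect 2, error 0.05 and 40 women per cluster.
- Clusters: 1.96² × 0.42 × 0.58 × 2 / (0.05² × 40) = 18.7.
- Women: 18.7163 × 40 = 748.7; × 1.10 = 823.5.
- Clusters to recruit: 823 / 40 = 20.6, so 21.

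The stated 748, 823 and 21 reproduce. They rest on cord care, not immunisation, so this point does not touch the sample size.

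**Assumptions.** The protocol gives neither the age distribution of the babies nor the timing of doses. I assume ages spread evenly over a window of W days, with W = 60 or W = 120 (four months), and vary the timing of doses.

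**Share of babies under 28 days = 28/W.**
- W = 60: 28/60 = 46.7%, about 384 of 823.
- W = 120: 28/120 = 23.3%, about 192 of 823.

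**Observed as a fraction of eventual uptake.** If doses are spread evenly from birth to day T and none follow, the ratio is 1 − T/(2W).

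| Doses spread over | W = 60 | W = 120 |
|---|---|---|
| all at birth | 1.00 | 1.00 |
| 7 days | 0.94 | 0.97 |
| 14 days | 0.88 | 0.94 |
| 28 days | 0.77 | 0.88 |
| 42 days | 0.65 | 0.83 |

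As an illustration with doses over 28 days, a true 70% would be read as 0.767 × 70 = 54% with the sixty-day limit, or 0.883 × 70 = 62% with the four-month limit. That is 16 or 8 points low.

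**Observed against uptake by day 28, when later doses exist.** Let U be true uptake by day 28 and V further uptake spread evenly over days 28-60, with W = 60.
- U = 60% spread evenly, V = 0: (28/60) × 0.60 × 0.5 + (32/60) × 0.60 = 46.0%, which is 14 points low.
- U = 60% all at birth, V = 20%: (28/60) × 0.60 + (32/60) × (0.60 + 0.10) = 65.3%, which is 5.3 points high.
- U = 30% spread evenly, V = 50%: (28/60) × 0.30 × 0.5 + (32/60) × (0.30 + 0.25) = 36.3%, which is 6.3 points high.

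The sign therefore depends on dose timing, which the form does not record.

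**What the age bands can do.** In completed weeks, the 2-4 band runs from day 14 to day 34 and the 5-8 band starts at day 35. Keeping the upper bands isolates babies of at least 35 days: with W = 60, 25/60 × 823 = 343. Babies aged 28-34 days cannot be separated from younger ones. Among those kept, a dose before day 28 cannot be told from a later one.

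**The case against.** Much of the case on the other side stands.

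- **Direction.** A reader might infer that the proportions are too low by construction. That holds only against eventual uptake, and not even there if every dose is given at birth. Against uptake by day 28 the examples above show errors of either sign.
- **Share of young babies.** A reader might also take it that nearly half the babies have not completed the neonatal period. The protocol contains no such figure. It needs an even age spread and the sixty-day limit; the four-month limit in the same section halves it.
- **Age is recorded.** It would be wrong to say the form cannot isolate babies past 28 days. The upper bands do so without any new field, at the price of days 28-34. Stratifying by band would also show how status changes with age. What remains missing is whether a dose came by day 28.
- **Postnatal visits.** The form records the timing of the first visit, so this item is not bare status to date. It needs only denominators of babies old enough for the interval reported, which is a minor matter.
- **Weight of the item.** Section 4.3.7 lists neither immunisation nor postnatal visits among the sub-study two variables. The trial outcome in section 4.4.7 is specified as immunisation within the neonatal period, with follow-up to four weeks, so it is largely unaffected.
- **Comparisons.** Mothers are drawn at random from enumerated lists, and nothing in the protocol suggests that maternal characteristics track the baby's age. Distorted odds ratios are a possibility, not something the documents show.

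A separate analysis plan, not shown, might set age-eligible denominators. It could not recover vaccination dates that the questionnaire never asked for.

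**Conclusion.** The point holds as a cheap improvement to sub-study two. Followed as written, the plan yields an immunisation proportion that depends on the age mix of the babies interviewed, for an element the protocol itself calls neonatal.

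The size rests on assumptions the documents do not supply. With evenly spread ages, 23% to 47% of babies are under 28 days, depending on which age limit applies. With doses spread evenly over 28 days and none later, observed uptake is 0.88 to 0.77 of the true value. The loss is nil if all doses are at birth and larger if they are spread over a longer period. Once doses after day 28 exist, neither the size nor the direction of the error against uptake by day 28 can be known from the data as collected.

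The damage is confined to the descriptive and association estimates for this item; the sample size is unaffected.

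**What to change.** 1. In section 4.3.6, reconcile the sixty-day and four-month limits, and bring Annex 5 and the age bands of Annex 6 into line with the result.
2. In Annex 6, record the baby's date of birth, the interview date and the vaccination dates, the last taken from the child card where one is held.
3. In section 4.3.8, report immunisation by day 28 among babies at least 28 days old at interview, counting doses up to day 28. Alternatively, use a time-to-event estimate with babies censored at their age at interview, which keeps everyone.
4. For postnatal visits, restrict each reported interval to babies old enough to have completed it.

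The cost is three kinds of date field. With the restricted denominator, the sample for this item falls to about 823 × 32/60 = 439 if ages are even over sixty days, or 823 × 92/120 = 631 if even over four months. The time-to-event version loses none.

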## Annex 7: Key Informant Interview guide with elderly caregivers and traditional birth attendant for sub study two

1. *Introducing the subject*

You have been a Traditional Birth Attendant/care provider for many years now; and for sure you have had a long experience working with pregnant women; conducting deliveries and caring for newborn babies. Today, I want to learn how care is provided for a pregnant woman here at home: before delivery, during the labouring process and how delivery is conducted here in the home, how the cord is handled and the other activities that people normally perform until the baby is two months old. What traditional rituals if any, are performed along this process?

1. *Climate setting*

How many years have you worked as a traditional birth attendant? How did you become a traditional birth attendant? Do you enjoy doing the work of a traditional birth attendant? How many deliveries have you conducted this year alone? Who invites you to conduct a delivery in the home? Do the family members come to you here or you go to the home of the labouring woman? What happens if it is in the night?

1. *Antenatal period (prohibition from eating some foods or engaging in certain activities)*

Sometimes pregnant women are advised not to eat certain foods or perform certain tasks while pregnant, what are the foods that pregnant women are not allowed to eat here in your village? Why are they stopped from eating these types of foods-does it harm them or harm the baby? (If there is none probe for what she has heard that is prohibited and why)

1. *During labour-intra-partum care*

When a pregnant woman goes in to labour where is she made to labour and deliver from? In the home-in the house, under the tree or a separate shelter is built purposely for the delivery? If it is during the day or at night (you are exploring for cleanliness and warmth and any traditional explanations for the actions)

During the delivery of the baby and when the baby has come out, what happens next? Who cuts the cord? At what stage is the cord cut? What instruments are used for cutting the cord? Who provides the instruments for cutting the cord-(the family of the labouring woman yourself) And how is the bleeding from the cord of the baby stopped?

1. *Post-partum*

What about the placenta-who delivers the placenta out of the woman’s womb? Please explain to me how this is done to make it come out of the woman. (in case hesitant probe-Do you have to pull it out or you wait for it to come out by itself)

At this stage that the cord is not yet cut and the baby is out what do you do with the baby? Where do you place him/or her? After the cord has been cut what happens with the baby? After delivering the placenta what happens with the placenta? And after delivery of the placenta what next do you do for the mother.

After all these the cord of the baby remains fresh for some days with a wound at the stump. Does this worry you at home? What is done to make the wound to heal properly?

Have you had any experience when sometimes babies come out when they are very tired-when you are the one assisting the pregnant woman with delivery how will you know that a baby is tired? And when you notice that the baby is tired, what actions do you take for the baby?

The baby is expected to feed-at what time do you start to feed the baby? Usually there is no breast milk at this time-what do you do feed for the baby

What advice do you give to the mother or attendant before leaving her to go home and rest?

Sometimes the newborn will fall sick (before reaching even one month)-have you had an experience when a newborn is sick? How can you notice that a newborn could actually be sick? What do you do for the parents of the sick baby and what do you do for the sick baby? What do other people do for such a sick newborn?

## Annex 8: Interview guide for In-Depth Interviews with sub groups of lactating women

The information we are interested in are the dos/do not; the care and advise received and from whom this support is coming.

1. Tell me about the pregnancy of this baby that you are carrying-how was it like
2. What about the labour and delivery-what are your memories about this event in your life
3. Tell me about the immediate post-natal period-what kind of services/support/advises did you receive for yourself and for the baby?

